### Participant timeline {13}

**Table Tabb:** 

	**STUDY PERIOD**					
	**Enrolment**	**Allocation**	**Post-allocation**			
**TIMEPOINT**	*** − t***_***1***_	**0**	***t***_***1***_	***t***_***2***_	***t***_***3***_	***t***_***4***_
**ENROLMENT:**						
**Eligibility screen**	X					
**Informed consent**	X					
**Teacher training**		X				
**Allocation**		X				
**INTERVENTIONS:**						
**Intervention:** **Second Step Early Learning (NOR ed.)**						
**Control condition: Free play**						
**ASSESSMENTS:**						
**SDQ** **(primary outcome)**			X		X	X
**EmQue** **(secondary outcome**			X		X	X
**Joint Attention Scale (mediator)**				X		
**Caregiver SES (moderator)**			X			
**Std. 1st grade screening test**						X

#### Sample size {14}

Our sample will consist of 990 children aged 4 to 5 years old, distributed in groups of > 15 per kindergarten. Our sample size calculation considered the following input parameters: (1) two groups in a cluster design with an allocation ratio of 1:1; (2) a minimal detectable effect size difference of *d* = 0.27, which is the upper limit confidence interval for the effect size reported on SEL skills derived from 114 studies [1], with a mean of 0.219 (95% CI = 0.171–0.267). In this meta-analysis, the most common measure used to track SEL was the *Strength and Difficulties Questionnaire* [27], which is our primary outcome measure and rated by teachers and parents. Such a difference of 0.27 is described as a small effect size, according to the traditional benchmarks proposed by Cohen [33]. When considering only the effect sizes among the youngest (called by Cipriano et al. [1]) as elementary schools (Kindergarten [5 years old] to 5th grade [10 years old]) from exclusively randomized controlled trials and using SEL skills as outcomes, the average adjusted effect size at post-assessment was 0.241 (derived from 96 effect sizes). Therefore, our minimum expected effect size is closer to the state-of-the-art. However, the effect sizes depend on the population, outcome, and nature of the implemented intervention. Researchers have recently used data from systematic reviews and meta-analyses to recalculate the cutoffs for the difference [34–36]. (3) Intraclass coefficient correlation-derived SDQ domains ranged from 0.015 to 0.064 [37]; (4) Power was 0.8, and the adopted significance level was 0.05.

A parallel, two-group cluster-randomized design will be used to test whether the Nor-SSEL (active intervention) mean is different from the Group “play” (active control) mean. The comparison will be made via a two-sided *t*-test with degrees of freedom based on the total number of subjects [38, 39], with a Type I error rate (*α*) of 0.05. The common subject-to-subject standard deviation for both groups is assumed to be 1, the intracluster correlation coefficient is considered to be 0.065, and the coefficient of variation of cluster sizes is assumed to be 0.65. For a power of 80%, with 30 kindergartens of 15 subjects per kindergarten in Group *Nor-SSEL* (totaling 450 children) and 30 kindergartens of 15 children per kindergarten in Group *Play* (totaling 450 subjects), the detectable mean difference (μ1 − μ2) is 0.27. Therefore, 900 children in 60 kindergartens are needed. To compensate for the potential decrease in power due to attrition, we will recruit 990 children from 66 kindergartens. The detectable difference was computed using PASS version 23.0.1.

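### The detectable difference uses degrees of freedom from 900 children although 60 kindergartens are randomised; with cluster degrees of freedom, 0.27 becomes 0.28

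*Protocol article*

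**What the plan says.** The Sample size {14} section of the protocol article sets out a parallel two-group cluster design. "The comparison will be made via a two-sided" t-test, "with degrees of freedom based on the total number of subjects", at a type I error rate of 0.05. Two methodological sources are cited for this and the software is named.

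The inputs are explicit:
- "The common subject-to-subject standard deviation for both groups is assumed to be 1"
- "the intracluster correlation coefficient is considered to be 0.065"
- "the coefficient of variation of cluster sizes is assumed to be 0.65"

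The result reads "For a power of 80%, with 30 kindergartens of 15 subjects per kindergarten" in each arm, 450 children per arm, and a detectable mean difference of 0.27. The section concludes that 60 kindergartens and 900 children are needed, and raises this to 66 and 990 to allow for attrition. The same section ties 0.27 to the upper confidence limit (0.267) of a meta-analytic estimate whose mean is 0.219.

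Sequence generation {16a} states that randomisation is at kindergarten level.

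**The concern.** Arm does not vary within a kindergarten, so the comparison of arms is made between kindergartens. With 30 per arm, the usual reference distribution is t with 60 − 2 = 58 degrees of freedom. Using the number of children gives 900 − 2 = 898, which is practically the normal distribution. The intracluster correlation and the coefficient of variation of cluster size enlarge the standard error. They do not correct the critical value, which is 1.963 with 898 degrees of freedom and 2.002 with 58.

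Two printed statements depend on this: that 0.27 is detectable with 80% power, and that 60 kindergartens are enough for it. Because 0.27 comes from the top of the cited interval, a detectable difference of 0.28 lies above the whole interval used to justify the design. The section also treats all six additional kindergartens as an allowance for attrition.

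**Working it through.** **Inputs**, all from Sample size {14}: two-sided α = 0.05, power 0.80, SD = 1, ICC ρ = 0.065, CV of cluster size = 0.65, mean cluster size m = 15, k = 30 kindergartens per arm (n = 450 children per arm).

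**Step 1: standard error.** The article does not say which correction for unequal clusters was used. The relative-efficiency form is taken here because it reproduces 0.27.

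- Equal-cluster design effect: 1 + (m − 1)ρ = 1 + 14 × 0.065 = 1.91
- λ = mρ / (mρ + 1 − ρ) = 0.975 / (0.975 + 0.935) = 0.5105
- Relative efficiency = 1 − CV² λ(1 − λ) = 1 − 0.4225 × 0.5105 × 0.4895 = 0.894
- Design effect = 1.91 / 0.894 = 2.1355
- SE = √(2 × 2.1355 / 450) = 0.0974

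**Step 2: reproduce the plan's figure.** Power is taken from the noncentral t distribution with noncentrality 0.27 / 0.0974 = 2.77. With 898 degrees of freedom, power at 0.27 is 79.1% and the difference detectable with 80% power is 0.273, which rounds to the printed 0.27.

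Two other variance formulas were tried with 898 degrees of freedom, and neither gives 0.27:
- Ignoring unequal sizes (design effect 1.91): detectable difference 0.258.
- 1 + [(1 + CV²)m − 1]ρ = 2.322: detectable difference 0.285.

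**Step 3: change only the degrees of freedom.**

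| Degrees of freedom | Detectable difference at 80% | Power at 0.27 |
|---|---|---|
| 898 (children) | 0.273 | 79.1% |
| 58 (kindergartens) | 0.278 | 77.8% |

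**Step 4: split the gap from 80%.** The total is 80 − 77.8 = 2.2 points. Degrees of freedom account for 79.1 − 77.8 = 1.3. The remaining 80 − 79.1 = 0.9 is already present under the plan's own settings and comes from rounding 0.273 to 0.27.

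**Step 5: kindergartens needed at 0.27.** With 2k − 2 degrees of freedom and all else unchanged:

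| Kindergartens analysed | Children analysed | Power at 0.27 |
|---|---|---|
| 60 | 900 | 77.8% |
| 62 | 930 | 79.2% |
| 64 | 960 | 80.5% |
| 66, no loss | 990 | 81.7% |
| 66, about 13.6 children each | 900 | 79.8% |

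So 64 kindergartens are needed for 80% at exactly 0.27, which leaves 66 − 64 = 2 in reserve.

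**Step 6: dependence on the inferred formula.** Under the larger design effect of 2.322, power at 0.27 is 75.6% with 898 degrees of freedom and 74.3% with 58. The level moves, but the loss from the degrees of freedom is again 1.3 points.

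**The case against.** The strongest reply is that nothing was miscalculated. The degrees-of-freedom rule is disclosed, sources are cited for it, and under those settings the figure reproduces. That stands: this is a declared method option, not a slip in arithmetic, and the cited sources cannot be checked here. It does not make the option suitable for a contrast between kindergartens.

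A second reply is that the calculation is conservative elsewhere. The ICC of 0.065 lies just above the cited range of 0.015 to 0.064. A CV of 0.65 looks large when each kindergarten must supply at least 15 children. The planned mixed model on three repeated scores may gain precision from baseline that an unadjusted t-test does not credit. As sensitivity values not found in the article, power at 0.27 with 58 degrees of freedom would be 82.4% at an ICC of 0.05, and 81.3% at a CV of 0.3. This also stands, and it shows that the effect of the degrees of freedom is smaller than plausible movement in either input. It does not rescue the printed figure, which is stated under the plan's own inputs; arm also remains a kindergarten-level factor in the mixed model.

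Three stronger readings might be inferred, and the article supports none of them:
- **That the degrees of freedom explain the whole drop from 80% to about 78%.** Step 4 shows that they explain 1.3 of the 2.2 points.
- **That clustering was ignored.** It was not; the variance carries a design effect of about 2.14.
- **That the trial's inference will use subject-based degrees of freedom.** The phrase occurs only in the sample size section. Statistical methods {20a} does not adopt it.

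**Conclusion.** The point holds as a minor one. The calculation uses a reference distribution that is slightly too favourable for a kindergarten-level comparison. Correcting it moves the detectable difference from 0.273 to 0.278, which changes the printed value from 0.27 to 0.28, and lowers power at 0.27 from 79.1% to 77.8%.

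The practical consequence lies in the reserve. If 0.27 remains the target, four of the six additional kindergartens are needed to reach 80%, so two are left for attrition. It would go too far to call the trial underpowered: with 66 kindergartens and no loss, power at 0.27 is 81.7%. It would also go too far to say that recruitment is unaffected whatever the target, because that holds only if 0.28 is accepted or losses stay small.

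The size of the degrees-of-freedom effect is firm. The exact power levels rest on the inferred correction for unequal clusters.

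**What to change.** Rerun the calculation with degrees of freedom based on the number of kindergartens, and name the correction used for unequal cluster sizes. Restate the result in Sample size {14}: 60 kindergartens of 15 children give 80% power for a difference of 0.28, and about 78% for 0.27.

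Add that 80% power at 0.27 takes 64 kindergartens (80.5%), and describe what the recruited 66 then provide: 81.7% with no loss, and 79.8% if all 66 remain but 900 children are analysed. The investigators can then choose openly between accepting 0.28 as the detectable difference and keeping 0.27 with a reserve of two kindergartens.

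The cost is one recalculation, a few sentences and a slightly less favourable stated figure. The planned 66 kindergartens need not change unless 0.27 is kept and a larger attrition reserve is wanted.

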### Eligibility criteria {10}

To be eligible for this study, kindergartens cannot have implemented an active Nor-SSEL intervention in their kindergarten for at least the past 4 years from the start of this study and are currently “naïve” to Nor-SSEL implementation. The minimum number of 4- to 5-year-old participants we seek per kindergarten is 15. Children will participate in either the intervention or control condition as part of the pedagogical setting in the kindergarten, regardless of their involvement in the research study (i.e., data collection).

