### Concealment mechanism {16b}

Our team of recruiters will lead the workshops and will be blinded to a random list of 66 elements created by someone external to the Norwegian team before the workshops. This list will be kept in a sealed envelope stored in a safe in the USA at Yale University. After the workshop with the kindergarten leader, the kindergarten names will be organized into a list. Kindergarten leaders will return to their kindergartens to discuss the project with parents. After parents’ approval and the baseline assessment, with a minimum of 15 children, is completed by the parents and teachers, the kindergarten and research team will receive a notification about the assignment status based on the previously randomized sequence order and the completion of the baseline assessment via our online system. The system is automated to identify when the information of the 15 children is available, and only after that will the system assign the arm status based on a randomly generated list. Recruiters, hence, cannot predict the next allocation. Simple randomization and blinding of the recruiters are intended to eliminate selection bias [41].

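### A mean of 15 per kindergarten, an enforced minimum of 15 and a cluster-size CV of 0.65 cannot all hold; the inconsistency is conservative, but the sample-size figures need restating

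*Protocol article*

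**What the plan says.** All of this is in the protocol article.

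- **Sample size {14}, calculation.** There are 30 kindergartens of 15 children per arm, so 450 + 450 = 900 children in 60 kindergartens. To allow for attrition, 990 children in 66 kindergartens will be recruited. The ICC is 0.065, and "The common subject-to-subject standard deviation for both groups is assumed to be 1". On spread of sizes: "the coefficient of variation of cluster sizes is assumed to be 0.65". The test is a two-sided t-test "with degrees of freedom based on the total number of subjects". The stated detectable difference at 80% power is 0.27.
- **Sample size {14}, opening.** The 990 children are "distributed in groups of > 15 per kindergarten".
- **Eligibility criteria {10}.** "The minimum number of 4- to 5-year-old participants we seek per kindergarten is 15".
- **Concealment mechanism {16b}.** Baseline must be complete "with a minimum of 15 children" before the kindergarten is told its arm, and the online system enforces this. Implementation {16c} repeats the condition.

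No section gives an expected mean above 15, a cap on enrolment, or a reason for a CV of 0.65.

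**The concern.** Both totals imply a mean of 15, since 900/60 = 990/66 = 15. The allocation rule makes 15 the smallest size a randomised kindergarten can have. If no value lies below the mean, none can lie above it, so every kindergarten has exactly 15 children and the CV is 0. A CV of 0.65 at mean 15 means an SD of 0.65 × 15 = 9.75 children, which requires some kindergartens well below 15. Those kindergartens would never trigger allocation.

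The published detectable difference therefore rests on a distribution of sizes that the trial's own rule excludes. Behind this lies an open design question: does enrolment stop at 15, or are all consenting children taken? The answer sets the total number of children, the data-collection load and the precision to be reported.

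**Working it through.** **Inputs (Sample size {14}).** Two-sided α = 0.05, power 0.80, SD 1, ICC ρ = 0.065, mean size m = 15, CV 0.65, k = 30 kindergartens per arm, degrees of freedom from subjects (898).

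**Formulas.** With L = mρ/(mρ + 1 − ρ), the design effect for unequal clusters is DE = [1 + (m − 1)ρ] / [1 − CV²·L(1 − L)]. The standard error is SE = √(2·DE/(k·m)). The detectable difference is about (1.960 + 0.842)·SE.

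**1. The plan's own figure.** L = 0.975/1.910 = 0.5105 and L(1 − L) = 0.2499. DE = 1.91/(1 − 0.4225 × 0.2499) = 2.136. SE = √(2 × 2.136/450) = 0.0974. The detectable difference is 0.2729 by the normal approximation and 0.2732 by noncentral t, which rounds to 0.27. Power at exactly 0.27 is 79.1%. The stated figure reproduces. The other common formula, 1 + [(CV² + 1)m − 1]ρ = 2.322, gives 0.285 and does not reproduce it.

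**2. Exactly 15 per kindergarten, CV 0.** DE = 1 + 14 × 0.065 = 1.91.

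| Kindergartens | Children | SE | Detectable difference | Power at 0.27 |
|---|---|---|---|---|
| 60 | 900 | 0.0921 | 0.258 | 83.3% |
| 66 | 990 | 0.0879 | 0.246 | 86.7% |

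With cluster-based degrees of freedom (58), the first row becomes 0.263 and 82.2%.

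**3. Minimum 15, open above, CV 0.65.** The mean must exceed 15, by an amount that depends on the shape of the distribution. The documents give no shape, so these are assumptions. If the largest size is M, the variance is at most (M − μ)(μ − 15), and the smallest possible mean μ solves √[(M − μ)(μ − 15)]/μ = 0.65. A shifted exponential has SD = μ − 15, so μ = 15/0.35.

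| Assumed sizes | Mean | Total in 66 | Detectable difference, 60 kindergartens | Power at 0.27 |
|---|---|---|---|---|
| Largest 100, smallest possible mean | 16.35 | 1,079 | 0.267 | 81% |
| Largest 60, smallest possible mean | 18.47 | 1,219 | 0.260 | 83% |
| Shifted exponential from 15 | 42.86 | 2,829 | 0.222 | 93% |

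With a largest size of 50, CV 0.65 cannot be reached (the maximum is 0.64).

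**4. Can attrition supply the CV?** The allowance is six whole kindergartens of 15, so the other 60 still average 15. If loss is instead by child, 900/66 = 13.6 with sizes at most 15. The CV then cannot exceed √[(15 − 13.6) × 13.6]/13.6, about 0.32, and random loss gives about 0.08.

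**5. Groups larger than 15.** Read literally, this needs at least 16 × 66 = 1,056 children, not 990.

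**The case against.** The strongest reply is that the calculation is correct and cautious: 0.27 follows from the stated inputs, and planning on the guaranteed 15 per kindergarten plus an allowance for unequal sizes is a familiar choice. Recruitment is counted in kindergartens, and 66 stands either way. Every consistent resolution checked, with the protocol's own subject-based degrees of freedom, gives a detectable difference at or below 0.27. All of this stands. What it does not do is make the inputs agree. The protocol never presents CV 0.65 as a deliberate margin, and 990 is too low if sizes vary above 15.

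Two further defences are weaker. The eligibility sentence, taken alone, could describe a target; but the concealment and implementation sections make 15 complete baselines a condition of assignment. The wording about groups larger than 15 may be a slip for at least 15, or a symbol lost in text extraction. It is a wording point to align, not a demand for 1,056 children.

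A reader might also infer that the trial needs some 2,800 children, or that most kindergartens would fall below the minimum. The documents support neither: both depend on a chosen distribution, and other shapes reach CV 0.65 with about 1,080 to 1,220 children.

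**Conclusion.** The inputs are mutually inconsistent, and this is exact: it needs no distributional assumption. The stated 0.27 reflects CV 0.65. At exactly 15 per kindergarten the figure is 0.258 (60 kindergartens) or 0.246 (66). If enrolment is open above 15 with CV 0.65, the total exceeds 990 by an amount the documents do not fix.

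A reader might infer an arithmetic error or an underpowered trial. Neither follows. The arithmetic from the stated inputs is right, and the discrepancy runs in the trial's favour: the resolutions checked give 0.22 to 0.267 at 60 kindergartens. These sizes assume ICC 0.065, SD 1, the design-effect formula that reproduces the plan's figure, and subject-based degrees of freedom. The point is a correction to stated figures that should be made; it does not call the design into question.

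**What to change.** State which enrolment rule applies, and give one consistent set of figures.

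- **Capped at 15:** use a CV near 0 and report a detectable difference of about 0.26 with 60 kindergartens. The total of 990 in 66 stands.
- **Open above 15:** give the expected mean, its CV, and the total and detectable difference that follow from them. The planned number of children must then be restated upward.

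In both cases make the sample-size wording (larger than 15), the eligibility and concealment wording (minimum of 15) and the total of 990 agree.

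The cost is a short recalculation and edited text. The number of kindergartens need not change. Under open enrolment the extra children also bring extra questionnaires. Trial status describes this version as not yet recruiting, so the correction could be made at that stage at little cost.

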### Recruitment {15}

We have a designated team that actively recruits kindergartens through various means, including letters, emails, advertising, student networks, and other methods, until we reach the calculated number of kindergartens. This approach involves contacting municipalities and inviting as many kindergarten leaders as possible to a gathering workshop scheduled for March 2026. During this workshop, we will introduce the project’s aims and team. Ultimately, those leaders interested in participating in the study will sign up for an intention list. If more than 66 leaders show interest, a random selection will be used to select only 66, and then a randomization for each arm of the study will be conducted in front of every individual using a true random generator. If fewer than 66 leaders sign up, a new event will be scheduled in a different region until the number of 66 is achieved.

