#### Assignment of interventions: allocation

### Sequence generation {16a}

We will use simple randomization at the kindergarten level. A random list of 66 elements will be created externally via Efron’s biased coin [40] implemented in PASS, where half of the numbers will be Nor-SSEL and the other half will have additional play time.

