### Implementation {16c}

After our workshops, we will send the names of the kindergartens to the software developer, [name], and [name] to register the potential kindergartens included in the system. Then, a notification will be sent to the kindergarten leaders, notifying them that they are invited and requesting their consent from parents. As soon as parents’ consent to their children’s participation, the baseline assessment of outcomes is implemented in the system, among parents and teachers. These steps and procedures ensure that the baseline assessment is fully completed before randomization, thereby avoiding the implementation in the kindergarten with incomplete baseline data. Once the data from the 15 children per kindergarten is completed, the system will allocate the random sequence previously generated by CC. Recruiters, hence, cannot predict the next allocation. The system will display, in real time, the project team and other kindergartens participating, the number of kindergartens that have already received an assignment (without disclosing the Nor-SSEL or additional playtime status) and the number of available spots for participation in the study. This measure aims to demonstrate the transparency of the study recruitment process, given that we have limited spots available. Additionally, this procedure will prevent delays in recruitment, motivate the kindergartens to submit their data as soon as possible, and allow them to be included promptly.

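### The recruitment section describes an open draw to arms and the schedule puts baseline after allocation; both contradict the protocol's own concealed, post-baseline allocation

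*Protocol article*

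**What the plan says.** The protocol article describes assignment to arms in several places.

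- **Recruitment {15}.** At a gathering workshop, "those leaders interested in participating in the study will sign up for an intention list". If more than 66 are interested, 66 are picked at random, after which "a randomization for each arm of the study will be conducted in front of every individual using a true random generator". When sign-ups fall short of 66, another event is held in a different region; no open draw is mentioned for that case.
- **Sequence generation {16a}.** The method is called simple randomization. The list of 66 is made externally with Efron's biased coin in PASS, "where half of the numbers will be Nor-SSEL and the other half will have additional play time".
- **Concealment mechanism {16b}.** The list is made before the workshops and kept sealed. Leaders return from the workshop to discuss the project with parents. After parental approval and baseline on at least 15 children, "the kindergarten and research team will receive a notification about the assignment status based on the previously randomized sequence order".
- **Implementation {16c}.** "These steps and procedures ensure that the baseline assessment is fully completed before randomization".
- **Who will be blinded {17a}.** Researchers do not know the assignment until baseline is assessed. Teachers and parents, the primary informants, are not masked.
- **Participant timeline {13}.** Eligibility screening and informed consent are at -t1. Allocation and "Teacher training" are at timepoint 0. The SDQ row ("primary outcome") and the EmQue row have their first mark at t1, and SES its only mark there. The t1 column stands under "Post-allocation". Outcomes {12} labels baseline as T1.

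**The concern.** In a cluster trial whose informants cannot be masked, the main protection against selective consent and coloured baseline ratings is that nobody knows a kindergarten's arm until consent and baseline are complete. Sections {16b} to {17a} provide that protection. The recruitment paragraph and the timeline each give an order of events that removes some or all of it.

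If the arm is known before parents are approached, the families who agree may differ between arms. If it is known before the baseline SDQ, teachers and parents may rate differently according to what they expect. That baseline score is one of the three repeated measures in the primary mixed model (Statistical methods {20a}), so a disturbed baseline enters the main analysis. Neither kind of damage can be repaired afterwards.

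**Working it through.** **Order of events, side by side**

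| Source | How the arm is determined | Relative to parental consent | Relative to baseline SDQ |
|---|---|---|---|
| Recruitment {15}, more than 66 interested | Live draw before those present, true random generator | Before | Before |
| {16a} to {17a} | Sealed external list, released by the system | After | After |
| Participant timeline {13} | Not stated | After (consent at -t1, allocation at 0) | Before (baseline at t1) |

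*Step 1: mechanism.* A live draw and a list fixed before the workshops cannot both determine the arm. At least one account is wrong as written.

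*Step 2: timing against consent.* {16b} places the discussion with parents after the workshop. A draw held at sign-up therefore comes before consent, whereas {16b} and {16c} put consent first. The timeline agrees with {16b} and {16c} on this.

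*Step 3: timing against baseline.* Baseline is T1 in Outcomes {12}. In the timeline t1 follows timepoint 0, and neither SDQ nor EmQue has a mark at -t1 or 0. The timeline therefore shows baseline after allocation, contrary to {16c}. Training is arm-specific: a play orientation in {6b}, Nor-SSEL training in {11a}. With training at 0 and baseline at t1, teachers would have been trained for their arm before giving baseline ratings.

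*Step 4: who is exposed.*
- Recruitment text followed, oversubscribed case: consent and baseline both take place with the arm known. If it governed the whole trial, that would be 66 × 15 = 990 children.
- Timeline followed: only the baseline ratings are exposed.

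**Lesser point: the method named in {16a}**

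Input: a list of 66 with two arms, from {16a}. Assumption: Efron's coin with p = 2/3, since the document gives no value.

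- Simple randomization: P(exactly 33:33) = C(66,33) / 2^66 = 0.098, about 10% of lists.
- Efron's coin: with r = p/(1 − p) = 2, the limiting probability of exact balance at an even list length is 1 − 1/r = 0.50. Exact recursion over 66 assignments also gives 0.50.

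Neither method guarantees the half-and-half split that the same section states.

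**The case against.** The strongest reply is that the intention is clear. The sections on concealment, implementation and blinding agree with one another, and {16b} and {16c} describe an automated gate that releases the arm only after baseline. The outliers are one sentence under Recruitment and one table. That stands: concealed post-baseline allocation is very probably what is meant. It makes this a matter of reconciling the text, and it would be wrong to infer that the trial has no concealment. It does not make the conflicting instructions harmless, because staff at the workshop or working from the schedule could follow them in good faith.

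Four stronger readings are tempting and are not supported:

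- *That every kindergarten would be drawn openly at the workshop.* The sentence is written for the case of more than 66 interested leaders, and it does not state where the draw takes place. The workshop is the natural inference from its position after sign-up and from the draw being held in front of everyone. If the draw applies only when oversubscribed, the allocation method would depend on turnout, which also needs correcting.
- *That the timeline unblinds consent.* It does not; consent is at -t1, before allocation.
- *That teacher training sharing the Allocation column is itself an error.* Row order within a column carries no timing, and {17a} has training follow allocation. The problem is only that t1 comes after both. The table was also read from PDF, so fine inferences from its layout deserve caution.
- *That the bias can be expressed as a share of the 0.27 SD detectable difference.* The document gives no basis for the size of a baseline shift, nor for assuming that it would pass one-for-one into the treatment effect under the longitudinal model.

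**Conclusion.** The point holds as an internal contradiction with real consequences. Recruitment {15} conflicts with {16a} to {17a} on both the mechanism and the timing of allocation. The timeline conflicts with {16b} to {17a} on the order of baseline and allocation. These are stated rules that disagree, so a fuller protocol or an analysis plan could not make both true.

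The exposure is bounded as follows: consent and baseline in the oversubscribed case if the recruitment text is followed, and baseline ratings alone if the timeline is followed. This rests on reading the open draw as held at or directly after sign-up, and on t1 in the timeline being the baseline named in Outcomes {12}. No numerical bias can be given.

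The wording of {16a} is a separate, secondary defect. Three descriptions that do not coincide are applied to one list, and exact balance would arise in about 10% of lists (simple) or about 50% (Efron's coin, p = 2/3 assumed). This must be corrected before allocation begins, because concealment once lost cannot be restored.

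**What to change.** 1. In Recruitment {15}, remove the open draw to arms. Let the workshop collect intentions and, if more than 66 leaders are interested, select 66 at random.
2. In Participant timeline {13}, move t1 (SDQ, EmQue, SES) ahead of the Allocation column and show teacher training after allocation.
3. Keep {16b}, {16c} and {17a} as the only allocation procedure, and refer to them from Recruitment.
4. In {16a}, name one restricted method that delivers 33:33, held externally, and drop the word simple there and in {16b}.

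The cost is a few sentences and one table edit, with no extra data, staff or sample size. The article's Trial status section says that the trial was not yet recruiting, and the workshop is scheduled for March 2026, so the change belongs before that event.
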